## Abstract

**Introduction::**

Halitosis is the term used to describe any unpleasant odor relative to expired air regardless of its source. The prevalence of halitosis in the population is approximately 30%, of which 80 to 90% of the cases originate in the oral cavity resulting from proteolytic degradation by gram negative anaerobic bacteria. Antimicrobial photodynamic therapy (aPDT) has been widely used with very satisfactory results in the health sciences. It involves the use of a non-toxic dye, called photosensitizer (FS), and a light source of a specific wavelength in the presence of the environmental oxygen. This interaction is capable of creating toxic species that generate cell death. The objective of this controlled clinical study is to verify the effect of aPDT in the treatment of halitosis by evaluating the formation of volatile sulphur compounds with gas chromatography and microbiological analysis before and after treatment.

**Materials and Methods::**

Young adults in the age group between 18 and 25 years with diagnosis of halitosis will be included in this research. The selected subjects will be divided into 3 groups: G1: aPDT; G2: scraper, and G3: aPDT and scraper. All subjects will be submitted to microbiological analysis and evaluation with Oral ChromaTM before, immediately after treatment, 7, 14, and 30 days after treatment. For the evaluation of the association of the categorical variables the Chi-square test and Fisher's Exact Test will be used. To compare the means the student *t* test and analysis of variance (ANOVA) will be used and to analyse the correlation between the continuous variables the correlation test by Pearson will be applied. In the analyses of the experimental differences in each group the Wilcoxon test will be used. For all analyses a level of significance of 95% (*P* < .05) will be considered.

**Discussion::**

Halitosis treatment is a topic that still needs attention. The results of this trial could support decision-making by clinicians regarding aPDT using aPDT for treating halitosis.

## Introduction

1

Halitosis is the term used to describe any unpleasant odor related to expired air regardless of its origin.^[1]^ The chemical components related to halitosis are volatile sulfur compounds (VSCs) such as hydrogen sulfide (H2S), methylmercaptanes (CH3SH), and dimethyl sulphide (CH3SCH3).^[2–5]^ The prevalence of halitosis in the population is approximately 30%, of which 80 to 90% of the cases originate in the oral cavity resulting from proteolytic degradation by gram negative anaerobic bacteria from sulfur-containing substrates in saliva, epithelial cells, blood, and food debris.^[6]^

The dorsum of the tongue and periodontal pockets are related as the major niches of bacteria that are responsible for the emission of VSCs. Some methods are used to diagnose halitosis: the organoleptic method, which is a subjective evaluation of the exhaled air of the mouth and nose, and a scale, is used to quantify this odor, depending greatly on the olfactory capacity of the evaluator. Sulphide monitors are devices that quantify the total value of VSC exhaled from the oral cavity. Gas chromatography is the most appropriate method to detect halitosis of different origins because it performs individual measurement of the three main gases (sulfhydride, methylmercaptanes, and dimethyl sulphide), allowing to assess the intensity of the breath and its origin. However, the lack of standardization in the protocol for diagnosis and treatment of halitosis makes it difficult to compare the epidemiological data obtained in different countries.^[7,8]^

Currently the treatment of halitosis is related to the masking of the odor or the decrease of the number of bacteria, through chemical and mechanical removal with the use of tongue scrapers and mouthwashes.^[5,9–13]^ Antimicrobial photodynamic therapy (aPDT) has been widely used with very satisfactory results in the health sciences. It involves the use of a non-toxic dye, called photosensitizer (FS), and a light source of a specific wavelength in the presence of the environmental oxygen. This interaction can create reactive oxygen species (ROC) that generate cell death.^[14–17]^ The advantages of this approach are to avoid resistance to target bacteria and damage to adjacent tissues as the antimicrobial effect is confined only to the areas covered by the photosensitizer and irradiated by light acting on the target organism rapidly, depending on the dose of light energy and power output. In addition, according to Wainwright, M.^[18]^ bacterial resistance to aPDT is unlikely, since the singlet oxygen and free radicals formed interact with various bacterial cell structures and different metabolic pathways.

Halitosis is considered one of the problems related to the impact of oral health on quality of life and is enough to affect the individual's perception about his life.^[19]^ Therefore, there is a need for new treatment alternatives for the patient, especially in the face of the technological advances in dentistry, so the patient's expectation regarding the final results can be met. The present study proposes to conduct a controlled clinical trial to evaluate the effectiveness of the application of aPDT in the tongue coating as a new way to control halitosis, mainly because it is a fast, non-invasive procedure and does not generate bacterial resistance.

## Materials and methods

2

The study will follow the regulatory norms of research in humans with favourable opinion of the Research Ethics Committee of the University Nove de Julho number, and the participants will sign the informed consent form after clarifications for authorization of the participation in the research, according to Resolution 466/12 of the National Health Council. Type of study: controlled, quantitative, cross-sectional clinical study.

### Hypothesis

2.1

Null hypothesis: There is no alteration of halitosis after the use of photodynamic therapy employing the use of blue dye and red LED. There is no microbiological alteration after antimicrobial photodynamic therapy. Experimental hypothesis: there is a decrease in halitosis after the use of photodynamic therapy using blue dye and red LED associated or not with the tongue scraper. There is microbiological alteration after antimicrobial photodynamic therapy.

### Research subjects

2.2

For this study, young adults of both sexes, students and employees of the *Universidade Nove de Julho*, São Paulo will be evaluated.

### Inclusion criteria

2.3

Young adults between the ages of 18 and 25, with an informed consent form and authorization for the diagnosis and treatment of halitosis. Young adults diagnosed with halitosis presenting Oralchroma S2H ≥ 112 ppb and/or CH3SH ≥ 26.

### Exclusion criteria

2.4

Individuals will be excluded from the study:

With dentofacial anomalies, in orthodontic and/or orthopedic treatment,Using a removable device, implant and/or prosthesis,With periodontal disease,With carious lesions,In cancer treatment,On antibiotic treatment up to 1 month before the survey,Pregnant,With hypersensitivity to the photosensitizer to be used.

As the research is a randomized clinical study and seeking greater transparency and quality of this research, we will use the CONSORT (Consolidated Standards of Reporting Trials) recommendations (Fig. 1). The protocol is in accordance with the 2013 Standard Protocol Items: Recommendations for Interventional Trials (SPIRIT) Statement.

**Figure 1 F1:**
[figure not shown]
Flowchart.

The selected subjects will be divides by block randomization into 3 groups (n per group = 13), according to the treatment to be performed. Opaque envelopes will be identified, and a sheet containing the information of the corresponding experimental group will be inserted. There will be a 1 session for each group (Table 1). All samples from the subjects will be submitted to microbiological analysis and evaluation with Oral ChromaTM before and after treatment, followed by controls of 7, 14, and 30 days.

**Table 1 T1:**
[figure not shown]
Experimental condition.

### Microbiological analysis

2.5

Samples of tongue coating will be collected using a sterile swab that will be passed on the surface of the tongue dorsum with a single movement and light pressure. Samples will be deposited in sterile tubes that will be identified and stored at -80°C until analysed. After thawing, the samples will be vortexed for 1 minute. For extraction of the bacterial DNA samples will be boiled for 10 minutes and then centrifuged at 10,000 rpm for 10 minutes. The supernatant will be placed in a new microtube containing 100 μL phenol/chloroform/isoamyl alcohol (25: 24: 1), followed by ethanol precipitation. The purified DNA will be resuspended in TE buffers. The levels of P. gingivalis, T. forsythia, and T. denticola will be analysed by quantitative PCR. The quantitative analysis will be performed using real-time PCR using the Step One Plus Real-Time PCR System (Applied Biosystem, Foster City, CA) and fluorescently detected products using the Quantimix Easy SYG Kit (Biotools, Madrid, Spain), following the protocol recommended by the manufacturer. To the reaction 10l will be used SYBR Green 0.5 ul DNA template, 200 mM of each primer (P. gingivalis CATAGATATCACGAGGAACTCCGA TT and AAACTGTTAGCAACTACCGATGTGG; T. forsythia GGGTGAGTAACGCGTATGTAACCT and ACCCATCCGCAACCAATAAA, T. denticola CGTTCCTGGGCCTTGTACA and TAGCGACTTCAGGTACCCTCG; Universal bacteria CCATGAAGTCGGAATCGCTAG and GCTTGACGGGCGGTGT) in total volume of 20 μl. For the standard curve, reactions containing template DNA 2 to 2X105 copies of the analyzed gene (16S rRNA) will be performed using pTOPO plasmids in which the 16S genes of the 14 different organisms will be cloned. As a negative control sterile milliQ water will be added instead of DNA template. Reactions to 16S rRNA will be performed with initial denaturation at 95°C for 2 minutes followed by 36 cycles of 94°C for 30 seconds, 55°C for 1 minute and 72°C for 2 minutes and final extension at 72°C for 10 minutes 46. Fluorescence will be detected after each cycle and plotted using Step One Plus Real-Time PCR System software (Applied Biosystem, Foster City, CA). To ensure the specificity of the products detected by fluorescence and to avoid detection of primer dimers, the detection will be performed to a degree below the dissociation temperature of the amplicons. All samples will be analyzed in duplicate and each dilution of the plasmids to the standard curve in triplicate. The purpose of the microbiological evaluation will be to verify the effectiveness of the photodynamic therapy for the treatment of halitosis, complementing the clinical evaluation.^[20]^

### Assessment of halitosis level

2.6

The literature describes some methods for measuring halitosis, such as the organoleptic assessment of air emanated from the oral cavity,^[21,22]^ by sulfide monitor^[21,23,24]^ and by gas chromatography.^[24–26]^ However, it has already been demonstrated that the organoleptic test can be influenced by the olfactory ability, the emotional state of the examiner and by climatic conditions. Therefore, the Oral Chroma portable device (Abilit, Japan) (Fig. 2), using a highly sensitive semiconductor gas sensor, will be used for this study.

**Figure 2 F2:**
[figure not shown]
Oral Chroma.

The air collection will follow the OralChromaTM Manual Instruction, in which the participant is instructed to make a mouthwash with cysteine (10 mM) for 1 minute to differentiate the VSCs origin and remain mouth closed for 1 minute. A manufacturer's own syringe for collection of mouth air will be introduced into the patient's mouth with the plunger fully inserted. The patient closes his mouth, breathes through his nose and waits with his mouth closed for 1 minute. They will be asked not to touch the tip of the syringe with their tongue. The plunger will be pulled out, re-emptied into the patient's mouth and pulled out again to fill the syringe with the breath sample. The tip of the syringe will be cleaned to remove moisture from the saliva, the gas injection needle will be placed in the syringe and the plunger will be adjusted to 0.5 ml. The air is injected into the door of the appliance in a single movement (Fig. 3).

**Figure 3 F3:**
[figure not shown]
Halimetry procedure.

OralChromaTM allows the capture of gas concentration values by measuring the VSC thresholds (from 0 to 1000 ppb), very accurately after 8 minutes. The results are stored on the device itself and can be retrieved and viewed at any time for comparison before and after treatment.

From the analysis of VSC captured by the system, we have:

Sulfide: originates mainly from the bacteria present on the back of the tongue. Values above 112 ppb are indicators of halitosis.Methylmercaptanes: predominantly higher in the periodontal pockets. Values up to 26 ppb are considered normal. Periodontal disease typically results in a high ratio of methylmercaptanes/sulfhydride (> 3:1)Dimethyl sulphide: may have periodontal or systemic (intestinal, hepatic, pulmonary) origin. It can also be caused, temporarily, by the ingestion of certain foods and beverages. The perception threshold of dimethylsulphide is the lowest, 8 ppb.

To avoid changes in halimetry, the examination will be conducted in the morning^[26]^ and participants will be instructed to follow the following guidelines: 48 hours before the evaluation, avoid ingesting food with garlic, onion and strong seasoning, alcohol consumption and use of oral antiseptic. On the day of the evaluation, in the morning, you can eat up to 2 hours before the examination, abstain from coffee, candies, chewing gum, oral hygiene products, and perfumed personnel (aftershave, deodorant, perfume, creams and/or tonic) and the tooth brushing should be done only with water.^[27]^

### Application of aPDT

2.7

For the photodynamic therapy, an equipment developed for this project will be used, with emission of red LED (660 nm) and tip of 2.84 cm^2^ in diameter. At the moment of application of the aPDT, only the volunteer to be treated and the professional responsible will be present, both using specific eye protection glasses. The active tip of the laser will be coated with clear disposable plastic (PVC) (avoiding cross contamination) and the professional will be properly dressed (Fig. 4). Methylene blue will be used as the photosensitizing agent, at a concentration of 0.005% (165 μm), to be applied in enough quantity to cover the middle third and back of the tongue for 2 minutes for incubation. The excess will be removed with a sucker in order to maintain the surface wet with the photosensitizer itself, without the use of water. Four points will be irradiated with 1 cm between them, considering the scattering halo and the effectiveness of aPDT (Fig. 5). Based on previous studies carried out with aPDT for the treatment of halitosis^[21–24]^ the apparatus will be previously calibrated with wavelength 660 nm, with energy of 36 J, power of 400 mW for Groups 1 and 3 that will be irradiated for 90 seconds per point, creep of 1039.4 mW/cm^2^ (Table 2).^[28]^

**Figure 4 F4:**
[figure not shown]
Implementation points for the aPDT. aPDT = antimicrobial photodynamic therapy.

**Figure 5 F5:**
[figure not shown]
Shows an adjustment of the power of the test as a function of the total sample size.

**Table 2 T2:**
[figure not shown]
Shows the radiometric and spectroscopic parameters of the equipment developed for this project.

The method of point application will be used in direct contact with the tongue.

### Sample calculation

2.8

For the calculation of the sample size, the data of the work by A. Costa Costa and Mota et al was used. Effect of photodynamic therapy for the treatment of halitosis in adolescents—a controlled, microbiological, clinical trial.^[29]^

Initially we established an error 

, where 

 and 

 are the baseline values for periodontal treatment with PDT. From this error, the effect size, given by

err/√ (σ_1 ^ 2 + σ_2 ^ 2)

where σ_1 ^ 2 and σ_2 ^ 2 are the variances of groups 1 and 2, respectively.

Assuming that the studied groups have a normal or approximately normal distribution, that the sample size will be sufficiently large and that a 2-tailed test will be used, for a significance level α = 0.05 and maintaining the power of the test 1-β = 0.90 we have: In Figure 5 it is observed that with a total sample size of 39 subjects, that is, 3 groups with 13 samples each, the statistical difference should be demonstrated, keeping the power of the test greater than or equal to 0.90. If the normal distribution hypothesis is rejected, the sample size should be corrected by approximately 5%.

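### The stated power of at least 0.90 with 39 subjects rests on a two-group formula with inputs described as baseline values, so it is not supported for any comparison among three arms of 13.

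*Protocol article*

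**What the plan says.** Section 2.8 (Sample calculation) takes its planning data from an earlier controlled trial of photodynamic therapy for halitosis in adolescents. It first sets an ‘error’, whose defining equation was lost when the text was extracted. The sentence explaining the symbols survives and says that they "are the baseline values for periodontal treatment with PDT".

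The error is divided by the square root of two summed variances, which "are the variances of groups 1 and 2, respectively". The section then assumes normality, and further "that the sample size will be sufficiently large and that a 2-tailed test will be used". The significance level is 0.05 and the target is given as "maintaining the power of the test 1-β = 0.90".

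The result is read from Figure 5, whose caption says that it plots power against total sample size. The section concludes that "with a total sample size of 39 subjects, that is, 3 groups with 13 samples each, the statistical difference should be demonstrated", with power at or above 0.90.

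Elsewhere, the randomisation paragraph under section 2.4 allocates 13 subjects to each of three groups. According to the abstract, these are aPDT, scraper, and aPDT plus scraper. Section 2.9 plans t tests and analysis of variance for means, and the Wilcoxon test for differences within each group. Section 2.8 does not say which comparison, outcome or time point the 0.90 refers to.

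**The concern.** Two features of the surviving text do not fit the claim.

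- **The input.** Power for a treatment comparison needs a difference in the outcome after treatment, or in the change from baseline. Section 2.8 describes its inputs as baseline values. Between randomised arms the expected difference at baseline is zero. If the lost equation instead set baseline against a later value in the same subjects, the result would be a within-group change, which does not power a comparison between arms.
- **The structure.** A difference, two variances and a two-tailed test describe a comparison of two groups. The trial has three. A two-group calculation read at a total of 39 would mean about 19.5 per group, not 13.

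The description of the inputs also fits poorly with this trial. They refer to periodontal treatment, whereas section 2.4 excludes people with periodontal disease.

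At stake is how a null result between arms is read. A protocol which promises that the difference should be demonstrated at 0.90 invites readers to take non-significance as evidence of no effect. With 13 per arm, that reading would be safe only for very large differences.

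**Working it through.** **Inputs from section 2.8:** two-sided alpha 0.05; target power 0.90; total 39, as 13 per arm; effect index err/√(σ1² + σ2²). No numerical difference, variance or effect size is readable. The stated power therefore cannot be reproduced forwards. The check works backwards, finding the effect that gives 0.90 under each plausible reading and then the power this implies at 13 v 13. Below, d is the difference divided by a common SD, so with equal variances the index equals d/√2.

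**Reading A: 13 per arm came from the large-sample two-group formula.**
- Index = (1.960 + 1.282)/√13 = 3.242/3.606 = 0.899.
- d = 0.899 × √2 = 1.271.
- The t test planned in section 2.9 has 24 degrees of freedom, critical value 2.064 and noncentrality 1.271 × √(13/2) = 3.24. Its power is about 0.87, so the shortfall from 0.90 is small.

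**Reading B: 39 was the total for a two-group test (19.5 per group).**
- Large-sample formula: d = 3.242 × √(2/19.5) = 1.04. Power at 13 v 13 is Φ(1.038 × √6.5 − 1.960) = Φ(0.687) = 0.75.
- t test: d = 1.07. Noncentrality at 13 v 13 is 1.066 × √6.5 = 2.72, and power is 0.74.

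**Reading C: 13 per arm came from an exact two-sample t test.**
- d = 1.33. Noncentrality is 1.326 × √6.5 = 3.38, and power is 0.90. The claim would hold for one unadjusted pairwise comparison.

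**Reading D: the curve is for a three-group F test with total 39.**
- f = 0.594. Noncentrality is 39 × 0.594² = 13.8 on 2 and 36 degrees of freedom, and power is 0.90. The claim would hold for the overall test.
- In SD units this is 0.594 × 3/√2 = 1.26 if one arm differs from two equal arms, or 0.594 × √6 = 1.46 between the extremes if the arms are equally spaced.
- The two-variance index and the two-tailed test do not describe an F test.

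**Reading E: a paired within-arm test on 13 subjects.**
- A mean change of 0.98 SD of the changes gives 0.90. This is not a comparison between arms.

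| Reading | Effect giving 0.90 as planned | Power at 13 per arm |
|---|---|---|
| A. Large-sample formula, 13 per arm | d = 1.27 | 0.87 (t test, pairwise) |
| B. Two-group total of 39 | d = 1.04 to 1.07 | 0.74 to 0.75 (pairwise) |
| C. Exact t test, 13 per arm | d = 1.33 | 0.90 (pairwise) |
| D. Three-group F test, total 39 | f = 0.59 | 0.90 (overall test) |
| E. Paired, within one arm | 0.98 SD of change | 0.90 (within arm only) |

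**What 13 v 13 delivers for assumed effects** (illustrations, not taken from the documents; two-sided 0.05, unadjusted t test): d = 0.5 gives 0.23, d = 0.8 gives 0.50, d = 1.0 gives 0.69 and d = 1.33 gives 0.90.

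**The case against.** The strongest reply is that the defining equation and Figure 5 were both lost in extraction, so the calculation cannot be faulted unseen. The phrase giving three groups of 13 fits a per-arm result multiplied by three, or a three-group curve, as well as it fits a two-group total. Readings C and D then give 0.90. Reading E does too, and it matches both the null hypothesis of no alteration after therapy in section 2.1 and the within-group Wilcoxon test in section 2.9.

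Much of this stands, and it rules out several stronger conclusions that a reader might draw:

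- **That the trial is underpowered.** The spread across readings reflects missing inputs. It is not a demonstrated shortfall.
- **That the effect index is mis-scaled.** With n per group, the large-sample noncentrality is exactly √n times the index. An error of scale would depend on which curve was used, and the curve is not visible.
- **That no post-treatment value enters the calculation.** The symbols are blank, and only their description as baseline values survives.
- **That omitting multiplicity or dropout allowances is an error.** A condensed article commonly leaves these to the full protocol or analysis plan.

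The reply does not rescue the claim itself. The surviving words specify baseline inputs, two variances and a two-tailed test. Readings C and D still need a post-treatment difference between arms as their input, D contradicts the stated formula, and E concerns change within one arm.

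**Conclusion.** The concern holds in this form: power of at least 0.90 is asserted, but the stated basis does not establish it for any between-arm comparison. It is not shown to be false. Pairwise power implied by the two-group readings runs from about 0.74 (39 as a two-group total) through 0.87 (13 per arm from the large-sample formula) to 0.90 (exact t test at 1.33 SD). A three-group F test at f of about 0.59 would also reach 0.90 overall.

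These figures assume normal outcomes, equal variances, all 13 subjects per arm analysed and no multiplicity adjustment. The conclusion about the inputs rests only on the readable description in section 2.8. If the full protocol shows a post-treatment or change difference between arms with its SD, that part would be answered, but the comparison to which the power applies would still need naming.

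**What to change.** Keep 39 subjects and rewrite the paragraph in section 2.8:

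1. Re-derive the planning difference and SD from post-treatment or change values of the halitosis outcome in the source trial, and print both numbers.
2. Name the between-arm comparison, the outcome and the time point to which the power applies, and the test used to calculate it.
3. Replace the claim of 0.90 or more with what 13 per arm delivers. For one unadjusted pairwise t test at two-sided 0.05, that is 90% power only for a difference of about 1.33 SD. Give the power for the re-derived difference beside it.

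The cost is one paragraph and probably a less favourable stated figure. No extra patients are needed, and neither the allocation nor the visit schedule changes.
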